#### Coaching

All schools will receive coaching in *RR* [15, 16, 34, 35, 40]. All coaches will be trained to fidelity and in the school consultation process [46]. We will use a blended coaching model which includes semi-structured conversations around setting goals, creating plans, reviewing progress, and revising/refining plans. Coaching sessions will use a behavioral skills training (BST) approach that entails direct instruction, rehearsal, and feedback [47], and ensures consistent trainings across each research site. Coaching will take place at a convenient time for the participant and target one didactic skill from *RR* per session. The coach will first explain the skill, how it applies to autistic students or their classmates, and its importance in relation to the development of students’ social functioning. Subsequently, the coach will show educators how to use the targeted skill via visual supports and modeling. Then, educators will be asked to practice the skill via role-play, so the coach can provide immediate feedback. At the end of the session, educators will be asked to practice the skills with focal students in between coaching sessions. Practice will be reviewed at the next session.

#### School-based teams

We will use the same procedures as in coaching to conduct manipulation checks on school-based teams fidelity. School-based teams will focus on the school personnel implementing *RR*. Facilitators from the research team will: (a) create a trusting interpersonal context within which school-based teams feel comfortable to talk about what is and is not working to support *RR *use, (b) help identify whether preconditions for successful implementation leadership and climate are in place, (c) leverage existing school-based teams that support EBP implementation (e.g., Multi-tiered Systems of Support, Positive Behavior Interventions and Supports) [48], and (d) work with the school-based teams to use existing communication systems (e.g., staff meeting, email) or help establish a communication system to ensure all *RR *implementers are abreast of the implementation and sustainment plan and action steps. Monthly school-based teams sessions will be recorded on Zoom. Session attendance, composition, team stability, and individual participant contributions will be documented. School-based teams will be individualized to each school to address its specific implementation needs [16]. Table 3 outlines the school-based teams components.

**Table 3 Tab3:** TEAM Session Topics

Session	Month	Duration	Personnel	Session Topics
1	1	45–60 min	School Admin Teachers Educators	Meet with implementation teams and assign roles; identify barriers to *RR* implementation; use conjoint analysis with school personnel to clarify and prioritize barriers to *RR* implementation
2	2	45–60 min	School Admin Teachers Educators	Select and match implementation strategies to address identified barriers to *RR* implementation; rate the degree to which the strategy is integral to *RR* fidelity; only strategies with high impact and high feasibility will be matched to identified barriers
3	3	45–60 min	School Admin Teachers Educators	Create an implementation blueprint; organize the top-rated strategies into a 3-phase implementation blueprint (pre-implementation, implementation, sustainment) to provide a roadmap for the *RR* implementation effort

Using the CFIR domains, we will work with school-based teams to identify, prioritize, and rate implementation barriers on their feasibility and importance [33, 49]. We will present implementation strategies and their definitions [16, 50, 51] that directly address identified barriers to implementation to participants to review and rate feasibility. The research team also will rate the degree to which the strategy is integral to *RR* fidelity on a scale of “1” for low to “3” for high impact. We will then select and match appropriate implementation strategies, with high feasibility and impact to *RR* barriers. Last, we will help participants create an implementation plan for the implementation and sustainment phase to provide a roadmap for *RR *implementation [33].

### Measures

We will collect the measures below that align with the CFIR domains.

#### Demographics and context

School personnel will complete a demographic form. Teachers will document percent time and activities where the student is included in general education settings. School characteristics (e.g., school size, percent eligible for free lunch, racial/ethnic composition) will be obtained via school records. Caregivers will complete a demographic form on students.

#### Autism symptomatology

Autistic students must have an educational eligibility of autism (e.g., IEP) and a Social Communication Questionnaire (SCQ) [52] score ≥ 15. Caregivers will rate the student’s “lifetime” characteristics to support an autism classification (sensitivity = 0.93; specificity = 0.93).

#### Implementation outcomes

*Fidelity* (primary outcome). An observer-rated fidelity checklist will be used to measure *RR* fidelity*.* A masked observer will measure *RR* skill acquisition and quality of intervention delivery. Skill acquisition will be scored “0” for “no” and “1” for “yes” to determine whether educators use the *RR* component. The number of components will be totaled and used for analysis. Quality of *RR* delivery will be coded on a Likert scale from “1” (not well) to “5” (very well) for each *RR* component that was used. The average quality rating across all intervention components will be used for analysis. Observer-rated fidelity will be collected during recess. Observers will be trained to ≥ 90% percent agreement on each item.

#### Sustainment

The extent to which *RR* is sustained will be calculated using the Provider Report of Sustainment Scale (PRESS) [53] at T4 and T5. Internal consistency is high (α = 0.95).

#### Fidelity checks

We will use the *RR* coaching fidelity checklist and the school-based teams fidelity checklist. A proportion score will be calculated for each measure.

#### Acceptability

We will use the Acceptability of Intervention Measure [54], a 4-item instrument. Raters score items on a 5-point scale ranging from “Completely Disagree” to “Completely Agree.” Internal consistency (α = 0.89) and test–retest reliability were good (α = 0.83). *RR* will be the referent.

#### Costs

We will use activity-based costing, an approach to micro-costing consistent with the “ingredients approach,” [55, 56] to estimate the costs of coaching with or without school-based teams. We will determine costs from multiple perspectives including system/payors (i.e., state education agency, regional education service agency and district), organizational (e.g., school) and provider perspectives as these are the primary stakeholders in implementation efforts [57]. While an aggregated (e.g., societal) perspective remains the gold standard in economic evaluation, it may not provide sufficient information for understanding why implementation fails to achieve desired objectives [58, 59]. Determining implementation strategy costs from multiple perspectives is essential to data-driven decision-making about resource allocation for EBP implementation. We will track time and other costs related to key activities across implementation phases, consistent with previous research [57, 59, 60]. Implementation costs will include fixed, time-dependent and variable costs. With input from the research team and school system partners, we will identify key activities associated with coaching and school-based teams across implementation phases – and with *RR*. Example activities during the implementation phase, for example, will include initial training of educators, and coaching sessions. Cost data collection will include a qualitative component with open-ended items that ask respondents to identify resources, needs, and priorities related to coaching with or without school-based teams [61, 62]*.*

#### Student outcomes

*Peer engagement.* The Playground Observation of Peer Engagement (POPE) [63] will be used to capture peer engagement at T1-T5. The POPE is an interval coding system where a masked evaluator conducts a live 10-min observation in 1-min intervals during recess (i.e., observation for 40 s, coding for 20 s). Each interval is assigned one mutually exclusive engagement state that represents the majority of the interval (e.g., solitary, jointly engaged, etc.). Observers will be trained and considered reliable with a criterion α > 0.80 [64]. The POPE has been used to measure peer engagement in autistic students [8, 10, 65–67], and has demonstrated high levels of reliability across multiple sites [68].

*Friendship Survey* [69]. The Friendship Survey is a 5-item questionnaire that assesses students’ peer relationships, rejection, and social network inclusion, that has been reliably used with elementary-aged autistic students and their peers [7, 8, 10, 70–72]. Students will be asked: “Are there kids in your class who like to hang out together? Who are they?” to identify specific students within each classroom social network [73].

*Friendship Survey Coding*. Social network inclusion refers to the prominence or salience of each individual in the overall classroom social structure. Three related scores will be calculated: 1) the student’s “individual centrality” (the total number of nominations to any peer group within the classroom), 2) the group’s “cluster centrality” (the average centrality of the peer group), and 3) the student’s “social network inclusion” (salience in the classroom). Four levels of social network inclusion are possible: 1) isolated; 2) peripheral (connected to one or two classmates); 3) secondary (well-connected); and 4) nuclear (very well connected) [73]. Students who do not receive any peer nominations to a group are considered isolated. Students in the bottom 30% of the classroom are considered peripheral. Students in the middle 40% of the classroom are considered secondary, and students in the top 30% of the classroom are considered nuclear. Social network inclusion scores will be normalized on the most nominated student in the classroom and calculated using students’ individual centrality divided by the highest individual centrality score within the classroom to provide a continuous metric of students’ social network inclusion (range 0–1) (Fig. 3).

**Fig. 3 Fig3:**
[figure not shown]
Social network inclusion

*Social skills.*Teachers will rate students’ social skills using the Teacher Perceptions Measure, a 12-item questionnaire that uses a 3-point Likert scale to rate teachers’ perceptions of students’ social skills (1 = never, 2 = sometimes, 3 = very often). This measure has been used with autistic and allistic students, and has good internal consistency, ranging from 0.72–0.88 [8].

*Quality of Play.* Caregivers will rate the quality of their child’s playdates using a modified version of the Quality of Play Questionnaire (QPQ) [74], a 17-item measure that considers the frequency of playdates and the amount of conflict during interactions to quantify play quality.

#### Organizational mediators

*Implementation Leadership.*Educators will complete the School Implementation Leadership Scale (S-ILS) [72], a 21-item measure that assesses seven subscales of implementation leadership: knowledgeable (understanding of *RR* and implementation issues), supportive (support for *RR* use), proactive (anticipating and addressing challenges), perseverant (consistent and responsive to challenges), communicative (shares implementation related information with staff), has a vision/mission (oriented towards using *RR*), and available in implementing *RR* [39, 75]. The S-ILS is a psychometrically validated and reliable instrument (α = 0.95–0.98). Implementation leadership is scored using aggregate individual ratings to the school level.

*Implementation Climate*. Participating educators will complete the School Implementation Climate Scale (S-ICS) [76], a 21-item measure that assesses seven subscales of implementation climate: focus, educational support, recognition, rewards, use of data, existing supports, and *RR *integration [75, 76]. The S-ICS is a psychometrically validated and reliable instrument (α = 0.81–0.91; 39, 79). Implementation climate is scored using aggregate individual ratings to the school.

*Team Processes.* TEAM members will complete the Team Processes Survey (TPS) [77] short form, a 10-item self-report of team processes (mission analysis, goal specification, strategy formulation and planning, monitoring progress toward goals, systems monitoring, team monitoring and backup, coordination, conflict management, motivation, and confidence building, and affect management). Responses are structured on a 5-point Likert-type scale from “1” = not at all to “5” = to a very great extent. The TPS has good internal consistency (α = 0.82–0.85). Table 4 outlines the complete study timeline, including data collection timepoints.

**Table 4 Tab4:** SPIRIT Flow Diagram

Activity	Study Period				
	**T1**	**T2**	**T3**	**T4**	**T5**
Enrollment					
Eligibility screen	X				
Informed consent	X				
Randomization	X				
Interventions					
Coaching	X	X			
TEAM	X	X			
Measures					
Demographics	X				
Autism classification	X				
Fidelity	X	X	X	X	X
Sustainment				X	X
Acceptability	X	X	X	X	X
Cost	X	X	X	X	X
Peer Engagement	X	X	X	X	X
Social Network Inclusion	X	X	X		
Social Skills	X	X	X		
Implementation Leadership	X	X	X	X	X
Implementation Climate	X	X	X	X	X
Team Processes	X	X	X	X	X

### Data analysis

All subjects, once randomized, will be included in the intent-to-treat sample, and every effort will be made to collect all primary and secondary outcomes even if the participant (educator, school personnel, or student) does not engage in randomly assigned treatments.

#### Primary aim 1

Primary Aim 1 analysis will contrast coaching with school-based teams vs. coaching only on change in *RR* fidelity (primary outcome) and students’ peer engagement (secondary outcome) from T1-T5. Generalized linear mixed models (GLMM) will be used to analyze change in T1-T5 for *RR* fidelity and sustainment as well as peer engagement and from T1-T3 for all other social outcomes. Separate models will be fitted for each primary and secondary outcome and a piecewise-linear model with potential knot(s) at T2 and T3, will be used to model the temporal trajectories across the study as the trajectories of the outcomes may occur at the end of each semester. The analysis will fit a GLMM with fixed effects for the intercept, time, and a group-by-time interaction. The GLMM will include random effects for the intercept and time (slope) and model the correlation between the two random effects. All outcomes will be assessed for normality. If outcomes are non-normally distributed, other distributions will be assumed or transformations of the outcomes will be considered. The GLMM also can be extended to model the nesting effects (e.g., educators nested within schools or students nested within classrooms or educators). The GLMM will adjust for the following baseline measures X when evaluating the primary outcome—*RR* fidelity: site and years of experience at current position. For models evaluating student outcomes, the GLMM will adjust for X: site and child’s age. The primary aim contrast in this study is the between groups difference in change in outcomes from T1-T5 for *RR* fidelity and sustainment as well as playground engagement and between group differences in changes from T1-T3 for all other student outcomes.

#### Secondary aim 2

Secondary Aim 2 aims to evaluate whether implementation leadership and climate mediates the effect of coaching with school-based teams (vs. coaching only) on *RR *fidelity and student outcomes. We will extend the regression models from Primary Aim 1 to evaluate the mediation effect [78]. The analysis will result in estimates of and confidence intervals for the direct effects for coaching with school-based teams (vs. coaching only) on outcomes and the indirect effects of the strategies on outcomes via implementation leadership and climate.

#### Secondary aim 3

Secondary Aim 3 aims to explore whether child characteristics collected at T1 moderate the effect of coaching with school-based teams vs. coaching on primary outcomes. GLMM will be expanded to include a third order interaction term (and all lower order interactions) of child characteristics (age, gender, autism classification) with strategy group (coaching with school-based teams vs. coaching only) with time (T1-T3) to evaluate the moderation effect.

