### Procedures

Recruitment in schools will include an informational email and video about the study, *RR*, coaching, and school-based teams. We will meet with school administrators via Zoom to share study information, participation requirements, and answer questions. We will then meet with educators to obtain consent and subsequently ask teachers to send recruitment materials (electronic/paper) to caregivers of focal students and classmates to participate in the Friendship Survey. The results of the Friendship Survey will determine social network inclusion status (isolated, peripheral, secondary, and nuclear). We will invite classmates who are classified as isolated, rejected, or peripheral and who may need additional support at recess (*n* = 1–2 per school) into the study.

An independent statistician will randomize all schools. The randomization (coaching with school-based teams vs. coaching only) has equal assignment probability to each group. Randomization will be stratified on the number of educators who will deliver *RR* (educators = 2 vs. > 2). Unmasking of randomization will not be permissible.

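### The stated model covariates leave out the one factor on which school randomisation is stratified (2 vs more than 2 educators), so the test may be conservative

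*Protocol article*

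**What the plan says.** Procedures: "An independent statistician will randomize all schools", and the allocation "has equal assignment probability to each group". "Randomization will be stratified on the number of educators who will deliver" the intervention, with the cut at 2 vs more than 2. No other stratification factor is named.

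Data analysis, Primary aim 1: the mixed model has "fixed effects for the intercept, time, and a group-by-time interaction". The baseline covariates are then named outcome by outcome. For the primary outcome they are "fidelity: site and years of experience at current position". For the rest, "For models evaluating student outcomes, the GLMM will adjust for X: site and child’s age".

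Neither list contains the number of educators or the randomisation stratum, and the sections on Aims 2 and 3, missing data and sample size do not add it. Site is adjusted for although it is not named as a stratification factor.

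**The concern.** Stratified allocation balances the arms on the stratum, which lowers the true sampling variance of the treatment contrast when the stratum is prognostic. A model without the stratum counts the between-stratum difference as residual or school-level variance, so its standard error does not reflect that balance. Confidence intervals are then too wide and p-values too large.

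The factor is also cluster size. A recess with three trained adults may develop differently from one with two, so a relation with change in fidelity or engagement is plausible, though the article gives no evidence for one. The trial is planned at 80% power, so an avoidable loss of even a few points is worth preventing.

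**Working it through.** **Inputs from the article.** 55 schools; at least 2 educators per school (Participants); 121 educators in total; 98 evaluable educators for a slope difference of 0.15 at 80% power and 5% type I error; 10% attrition; 10% variance inflation for clustering (Sample size and power considerations). I assume a two-sided test.

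**The plan's own figure.** Inflating 98 for attrition and clustering gives 98 × 1.1 × 1.1 = 118.6 (119), 98 × 1.1 / 0.9 = 119.8 (120), or 98 / 0.9 / 0.9 = 121.0 (121). The stated 121 reproduces, and adding the stratum does not change it. The base of 98 cannot be checked because no SD is given. With 49 per arm it implies an SD of change of about 0.265, so the target of 0.15 is 0.15 / 0.265 = 0.57 SD.

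**Size of the strata.** 121 − 2 × 55 = 11, so at most 11 schools (20%) have more than 2 educators. If all 11 have three, they hold 33 of 121 educators (27%).

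**School-level correlation.** Mean cluster size is 121 / 55 = 2.2. An inflation of 1.10 implies an ICC of 0.10 / (2.2 − 1) = 0.083.

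**How much wider the standard error becomes.** Let d be the stratum difference in change, in SD units (an assumption). A school mean has variance 0.083 + 0.917/m, giving weights of 1.85 for m = 2 and 2.57 for m = 3. The total weight is 44 × 1.846 + 11 × 2.571 = 109.5, or 1.99 per school. The larger-team share of weight is 28.3 / 109.5 = 0.258, and 0.258 × 0.742 = 0.192. The ratio of the unadjusted to the correct standard error is √(1 + 1.99 × 0.192 × d²) = √(1 + 0.381 d²):
- d = 0.3: 1.02
- d = 0.5: 1.05
- d = 0.8: 1.12

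**Simulation.** 44 schools of two and 11 of three, stratified 1:1 allocation, ICC 0.083, one change score per educator, no attrition, weighted school-level analysis, 8,000 runs per cell. The treatment effect was set at 0.534 SD, which gives nominal 80% power with 121 / 1.1 = 110 effective educators.

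| Stratum difference in change (assumed) | Type I error, stratum omitted / included | Power, omitted / included |
|---|---|---|
| 0 SD | 0.050 / 0.050 | 0.78 / 0.78 |
| 0.3 SD | 0.046 / 0.050 | 0.78 / 0.79 |
| 0.5 SD | 0.040 / 0.049 | 0.75 / 0.78 |
| 0.8 SD | 0.027 / 0.048 | 0.71 / 0.79 |

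Before rounding, the power differences are 0.787 − 0.776 = 0.010 (0.3 SD), 0.783 − 0.753 = 0.030 (0.5 SD) and 0.787 − 0.708 = 0.080 (0.8 SD). The mean treatment estimate was the same with and without the stratum, to within 0.001 SD. The type I error rates agree with the ratios above: multiplying the critical value by 1.02, 1.05 and 1.12 gives levels of about 0.046, 0.041 and 0.030.

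**How large these assumptions are.** The stratum's share of educator-level variance in change is 0.198d² / (1 + 0.198d²), where 0.198 = 0.273 × 0.727. That is 1.8% at 0.3 SD, 4.7% at 0.5 SD and 11% at 0.8 SD. On this scale 0.5 SD is 0.13, close to the 0.15 the trial is powered to detect between arms.

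**The case against.** **Validity is not at stake.** A reader might infer that analysing without the stratum biases the estimate or makes a false positive more likely. It does neither: the estimate is essentially unchanged, and type I error stays at or below 5%. This stands in full.

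**The benefit of stratifying is not all lost.** The arms remain balanced on the factor, so the estimator keeps that gain. What is missing is its recognition in the standard error. This also stands.

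**A loss equal to 5–10% of the sample is not supported.** It would require the stratum to explain 5–10% of the variance, which means strata differing by about 0.5 to 0.75 SD. The relevant variance is also that of change, because the contrast is group-by-time. A factor that predicts only the level of fidelity is largely taken up by baseline and the random intercept. The article reports no relation with change, so the range must start at nil.

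**The article condenses a fuller plan.** An analysis plan could add the stratum without contradicting the article, which does not say its lists are exhaustive. This carries limited weight: the covariates are named separately for each outcome type, with no sign that they are examples, and a plan that followed them would repeat the omission. The possible extension to nesting within schools does not help either, because a school random effect treats the stratum difference as noise.

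**Conclusion.** The mismatch is clear from the text: the only named stratification factor is absent from every stated covariate list. The consequence is possible conservatism. Power falls by nothing at 0 SD, about 1 point at 0.3 SD, 3 at 0.5 SD and 8 at 0.8 SD. These figures rest on an assumed stratum effect on change, on the largest possible larger-team stratum (11 schools of three), on the ICC implied by the plan's 10% inflation, and on a simplified single-change analysis instead of the full piecewise model. Confidence is high that the factor is omitted and low on how much that costs. It is a worthwhile correction because including the term showed no visible loss even when the stratum had no effect.

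**What to change.** Add the randomisation stratum (2 vs more than 2 educators) and its interaction with time to the fixed effects of the Aim 1 models, first of all the primary fidelity model, or state why it is left out. The interaction is needed because the contrast is on change; a main effect alone would mainly adjust the intercept. The Aim 2 mediation models extend those of Aim 1 and would inherit the terms. In the exploratory Aim 3 moderation models they are optional.

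The cost is one line in the plan and two to four parameters: one for the stratum, plus one per time slope (one slope with no knot, three with knots at T2 and T3). The slope terms rest on at most 11 schools in the smaller stratum, which is a reason to keep the number of knots low. The article reports no participants enrolled as of September 2024, so on its own account the change could be pre-specified. The sample size is unaffected.
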